**Stage 1: Assess eligibility for trial**

1. Laboratory confirmed infection with Ebolavirus
2. Has no underlying condition that could jeopardise patient or staff safety.
3. Able to comply with protocol requirements
4. Not determined by treating physician to be for end of life care only
5. IV access possible
6. No use of any investigational product within 30 days prior to study enrolment or planned use during the study period
7. Aged 18 years or more ++
8. Not a late (recovering patient) transfer from another facility

**Stage 2: Assess eligibility for randomisation**

1. Not known to be pregnant ++
2. Agrees to stop breastfeeding if lactating
3. Agrees to use birth control methods for 3 months following discharge.

**Stage 3: Allocate treatment cohort**

- If  $n \leq$  treatment beds available
- If  $n >$  treatment beds available, undertake randomisation

**Stage 4: Allocate observation cohort**

- If  $n >$  observational beds available, undertake randomisation
- If  $n \leq$  observational beds available

**Flowchart Details:**

- Stage 1:** If any criterion is not met (NO), the patient receives standard care. If all criteria are met (YES), proceed to Stage 2.
- Stage 2:** If the patient does not agree to stop breastfeeding or use birth control (NO), they receive standard care. If they agree, obtain consent. If consent is not obtained (NO), they receive standard care. If consent is obtained, perform a pregnancy test if the patient is a female aged 15-49 years old.
- Stage 3:** If the patient is not pregnant and agrees to use birth control, allocate to the treatment cohort. If the patient is pregnant or does not agree to use birth control, proceed to Stage 4.
- Stage 4:** If the number of patients is greater than the number of observational beds available, undertake randomisation. If the number of patients is less than or equal to the number of observational beds available, allocate to the observational cohort.

To assess the feasibility and safety of dosing with TKM-130803 in an ETU, data on the first four enrolled patients will be assessed by the IDMC prior to opening enrollment to additional patients. These patients (termed the safety cohort) may be recruited from one or multiple study sites. Each patient will receive at least 3 doses before dosing of the next patient starts. If a patient dies prior to receiving 3 doses, recruitment of the next patient may occur earlier. The IDMC will review data according to the schedule in Table 1 below. If the 4th patient dies prior to receiving 3 doses, the IDMC review may be brought forward. The safety cohort may be expanded following advice from the IDMC.

Page 15 of 37

|           |   |   |   |   |   |   |   |   |   |   |   |   | IDMC |   |   |   |
|-----------|---|---|---|---|---|---|---|---|---|---|---|---|------|---|---|---|
| Patient 1 | X | X | X | X | X | X | X |   |   |   |   |   |      |   |   |   |
| Patient 2 |   |   |   | X | X | X | X | X | X | X |   |   |      |   |   |   |
| Patient 3 |   |   |   |   |   |   | X | X | X | X | X | X |      |   |   |   |
| Patient 4 |   |   |   |   |   |   |   |   |   | X | X | X | X    | X | X | X |
| Patient 5 |   |   |   |   |   |   |   |   |   |   |   |   |      | X | X | X |
| Patient 6 |   |   |   |   |   |   |   |   |   |   |   |   |      | X | X | X |

*\*Patients 5 and 6 are recruited once recruitment is open following review by the IDMC.*

### 7.5. Participant inclusion criteria

The eligibility is a two-step process, first for the trial and then for the allocation to the drug eligible and observational cohorts. Patient ages <18 years will be excluded from both TKM treatment and observational cohorts until subsequent time as the IDMC recommends otherwise.

#### Eligibility criteria for the trial (stage 1):

##### Inclusion criteria

- Laboratory confirmed infection with Ebolavirus
- Adult aged  $\geq 18$  years (although the age range may be extended to >5years old following IDMC review of initial findings).
- Has no underlying condition that could jeopardize patient or staff safety
- Able to comply with protocol requirements
- Not determined by treating physician to be for end of life care only.
- IV access possible
- No use of any investigational or non-registered product within 30 days prior to study enrolment or planned use during the study period.

##### Exclusion criteria

- Determined, through a collaborative decision between the TCL and ETC medical lead, to be clinically recovering .

#### From within this cohort, additional inclusion criteria for randomization to the TKM cohort (stage 2):

- Not pregnant (although this might change after TSC review of the first 15 patients)
- Not breastfeeding (for lactating women)
- Agrees to use birth-control for 3 months post study.

The study of TKM treatment will concern the outcomes of all patients who are allocated to TKM treatment. For these patients, D1 will be the day of admission to the treatment centre. The primary response for the trial will be survival to D14 (yes or no). Patients who are allocated to TKM treatment and survive the first 48 hours after admission but do not actually receive it or who fail to complete the course of therapy, for any reason, will nevertheless be included in this primary analysis.

The observational study will include those considered eligible for TKM treatment but who are not allocated to it due to the limited number of available treatment beds or those patients otherwise eligible for the

study but do not comply with stage 2 of the eligibility criteria, up to the maximum number of available observational beds. For the analysis of the outcomes of these patients, D1 will be the day of admission to the treatment centre.

Data from participants who for any reason are ineligible for the trial or refuse to participate will be included (anonymously) in the primary analysis of the observational group. All patient outcome data is routinely recorded in all ETCs and shared anonymously with WHO, therefore the use of anonymised D14 outcome data is in line with current practices.

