## **7.2. Trial design rationale**

Due to production capacity limits there are currently only 100 treatment courses of TKM-130803 available for this trial.

The risk of infusion reactions means that TKM-130803 must be infused over a minimum 2-hour period during which clinical monitoring for infusion reactions is necessary. The intensity of clinical monitoring required means that infusions will, in most cases, only be undertaken in the morning (when the day shift of clinical staff and the trial staff are all on site). Even then, the challenges of clinical care delivery within an ETC means that the number of participants who can take part in the study, either receiving TKM-130803 infusions or in the observational cohort, and be safely monitored on any one day may be limited by staffing availability. ETCs may also vary in their capacity to recruit study participants based on fluctuating patient-staff ratios, and inpatient numbers. Therefore, the maximum number of patients receiving TKM-130803 on any one day, and the total number of observational patients, will need to be capped. The lead physician at the ETC will notify the maximum number of monitored beds available for the trial on any given day. Once the bed availability is known, if the number of patients eligible for TKM-130803 exceeds capacity they will be allocated to receive either the drug with standard care (as part of an interventional group) or standard care (as part of an observational cohort) or standard care. The methodology for allocating cohorts is described in section 7.3.

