4. Allocation into the observational cohort will occur by the following process.
  - i. Following arrival of the trial staff each morning, the maximal number of observational study beds (b) available for patients will be determined by the ETC clinical lead and the trial clinical lead.
  - ii. Patients who are eligible to receive study drug and have been randomised to the observational cohort will be again randomly allocated a number (n) from 1 to N, where N is the number of patients eligible (using a random number allocation program code in R statistical software).
  - iii. Patients will be allocated to the observational cohort by sequentially selecting patients by their number (n) from 1 to b. The remainder of patients will be put forward for standard care (when  $N > b$ ).
    - iv. If after randomisation there is one or more observational beds unallocated, randomisation of other patients identified as eligible for the observational cohort will be performed (e.g. patients that are not eligible for randomization into TKM, but only ever directly eligible for the observational cohort such as pregnant women). These patients will also be allocated a number (n) from 1 to N, where N is the number of patients eligible (again using a random number allocation program code in R statistical software).

```
graph TD
    subgraph Stage1 [Stage 1: Assess eligibility for trial]
        direction TB
        S1_1[1. Laboratory confirmed infection with Ebolavirus]
        S1_2[2. Has no underlying condition that could jeopardise patient or staff safety.]
        S1_3[3. Able to comply with protocol requirements]
        S1_4[4. Not determined by treating physician to be for end of life care only]
        S1_5[5. IV access possible]
        S1_6[6. No use of any investigational product within 30 days prior to study enrolment or planned use during the study period]
        S1_7[7. Aged 18 years or more ++]
        S1_8[8. Not a late (recovering patient) transfer from another facility]
    end

    subgraph Stage2 [Stage 2: Assess eligibility for randomisation]
        direction TB
        S2_1[1. Not known to be pregnant ++]
        S2_2[2. Agrees to stop breastfeeding if lactating]
        S2_3[3. Agrees to use birth control methods for 3 months following discharge.]
    end

    subgraph Stage3 [Stage 3: Allocate treatment cohort]
        direction LR
        S3_1[If n < or = treatment beds available]
        S3_2[If n > treatment beds available, undertake randomisation]

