    end

    subgraph Stage4 [Stage 4: Allocate observation cohort]
        direction TB
        S4_1[If n > observational beds available, undertake randomisation]
        S4_2[If n < or = observational beds available]
    end

    S1_1 --> S1_2
    S1_2 --> S1_3
    S1_3 --> S1_4
    S1_4 --> S1_5
    S1_5 --> S1_6
    S1_6 --> S1_7
    S1_7 --> S1_8

    S1_8 -- NO --> S1_Exit[Receive standard care. Include anonymised data.]
    S1_8 -- YES --> S2_1

    S2_1 --> S2_2
    S2_2 --> S2_3

    S2_3 -- "Obtain consent" --> S2_Exit[Insufficient operational capacity. Patient will receive standard care]
    S2_3 -- NO --> S2_Exit
    S2_3 -- "Pregnancy test if female aged 15-49 years old" --> S2_3_1[Pregnancy test if female aged 15-49 years old]
    S2_3_1 -- +ve result --> S4_1
    S2_3_1 -- -ve result --> S3_2

    S3_1 --> S3_Exit[Allocate to treatment cohort]
    S3_2 --> S4_1
    S3_2 --> S4_2

    S4_1 --> S4_Exit1[Insufficient operational capacity. Patient will receive standard care]
    S4_1 --> S4_Exit2[Allocate to observational cohort]
    S4_2 --> S4_Exit2
```

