## **9. DATA COLLECTION**

### **9.1. Clinical data acquisition**

Study dosing, sampling and data collection will begin after enrolment. Figure 3 shows the clinical data acquisition schedule.

Patient demographic data and medical history will be collected for all patients at the time of enrolment in the trial. While a participant is an inpatient, information will be collected daily on signs and symptoms, medications and blood products received, and the results of non-trial blood samples. For patients who are receiving TKM that day, detailed records of physiological monitoring and adverse event monitoring (outlined in section 8.2) will be provided.

SD1 (Study Day 1) is defined as the first day these data are collected. For patients who are in the TKM cohort this is likely to be the same day the first dose is administered.

These data will be collected daily for participating patients up to D14, or discharge, or death, whichever occurs first. Patients who achieve discharge criteria before D14 will stop the inpatient testing schedule upon discharge.

For patients not enrolled in the study, only anonymous survival data will be collected.

Discharge criteria are:

- 72 hours without fever or significant symptoms AND
- A significant improvement in clinical condition AND
- Able to feed, wash and walk independently AND
- Ebolavirus RNA PCR test negative

Figure 3: Clinical data acquisition procedures

[figure not shown]

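### Stage-1-eligible patients who get neither a TKM bed nor an observational bed are in no analysis, so bed capacity sets the patient mix behind the observational D14 mortality

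*Supplement*

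**What the plan says.** All references are to protocol v2.9.

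- **Cap.** Section 7.2 limits daily TKM numbers "and the total number of observational patients, will need to be capped". Section 7.5 repeats the limit: the observational study takes TKM-eligible patients without a treatment bed, and patients who meet stage 1 but fail stage 2, "up to the maximum number of available observational beds".
- **Who is left out.** Under section 7.4, step 4(ii), TKM-eligible patients not drawn for drug "will be again randomly allocated a number (n) from 1 to N". Under step 4(iii), those beyond the observational beds leave the study: "The remainder of patients will be put forward for standard care".
- **Order of priority.** Patients eligible only for observation, such as pregnant women, are considered later: "If after randomisation there is one or more observational beds unallocated" (step 4(iv)).
- **Who is added back.** Section 7.5 states that data from those "ineligible for the trial or refuse to participate will be included (anonymously) in the primary analysis of the observational group".
- **Data held.** Section 9.1: "For patients not enrolled in the study, only anonymous survival data will be collected".
- **Objective.** Section 6 gives the observational study its own primary objective, to describe early EVD mortality in a treatment centre. It is measured as D14 mortality among those alive 48 hours after admission.

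**The concern.** Section 7.5 divides patients who are not on TKM into three groups but gives an analysis role to only two. Those within the bed cap are in, and those who are ineligible or refuse are in. Those who are eligible and willing but without a bed are not mentioned. Read as written, the primary observational analysis counts all of the ineligible group and only a bed-limited share of the eligible group.

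The resulting mortality describes neither all patients off drug at the centre nor the TKM-eligible population. Its mix moves with daily staffing and caseload rather than with the disease. At stake are the observational primary result and any informal reading of TKM outcomes beside it.

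**Working it through.** The plan states no figure for the observational analysis, so there is none to reproduce. The check has two parts.

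**1. Where each group goes**

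| Patient off drug | Survival collected? | In observational primary analysis? |
|---|---|---|
| Stage-1 eligible, given an observational bed | Yes | Yes (7.5) |
| Fails stage 1, or refuses | Yes, anonymously (9.1) | Yes (7.5) |
| TKM-eligible, no bed in either cohort | Yes, anonymously (9.1) | Not assigned |
| Meets stage 1, fails stage 2, no bed | Yes, anonymously (9.1) | Not assigned |

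The last row does not fall under the add-back. In section 7.5, stage 1 is eligibility for the trial and stage 2 is eligibility for the TKM draw, so a stage 2 failure is still eligible for the trial.

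The two unassigned groups are lost in different ways. TKM-eligible patients are dropped by random number, which leaves the expected mortality among TKM-eligible patients unchanged. Stage 2 failures are dropped by priority because they get leftover beds only, so their loss is systematic.

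**2. Effect on the estimate**

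Let E be the eligible patients off drug, B those of them given an observational bed, and I the ineligible patients and refusers. Let mE and mI be D14 mortality in the eligible and the ineligible/refuser groups.

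- As written: (B·mE + I·mI)/(B + I)
- All patients off drug: (E·mE + I·mI)/(E + I)
- Difference: (mI − mE) × [I/(B + I) − I/(E + I)]

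The bracket is zero when B = E and positive whenever someone is squeezed out. The sign of the distortion is therefore the sign of mI − mE.

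Inputs: mE = 1 − 0.543 = 0.457, from the overall estimate in Table 3 (historical adults, omitting deaths on the day of admission and the next two days). E = 100, I = 50, B = 50 or 20, and mI from 0.20 to 0.80 are assumptions, because the documents give no counts and no mI. For simplicity one mE is used for all stage-1-eligible patients.

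The weight of the ineligible/refuser group should be 50/150 = 0.333. As written it is 50/100 = 0.500 with 50 beds, or 50/70 = 0.714 with 20 beds.

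| mI | All off drug | As written, B = 50 | Difference | As written, B = 20 | Difference |
|---|---|---|---|---|---|
| 0.20 | 0.371 | 0.328 | −0.043 | 0.273 | −0.098 |
| 0.30 | 0.405 | 0.378 | −0.026 | 0.345 | −0.060 |
| 0.457 | 0.457 | 0.457 | 0 | 0.457 | 0 |
| 0.60 | 0.505 | 0.528 | +0.024 | 0.559 | +0.054 |
| 0.80 | 0.571 | 0.628 | +0.057 | 0.702 | +0.131 |

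Differences are taken before rounding. With I = 25 and B = 50 the range is −0.034 to +0.046.

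**The case against.** Four points can be made for the plan.

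**It is a drafting slip.** Section 7.5 notes that treatment centres record all outcomes routinely, and section 9.1 collects survival on everyone not enrolled. The aim was plainly to use these outcomes, and the sentence was not updated when the cap was introduced. That is probably so, but an analyst who follows the written rule would still leave these patients out.

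**The random loss is harmless among TKM-eligible patients.** This stands for that group taken alone. It does not stand for the pooled figure, where the loss changes the weights, nor for stage 2 failures, whose loss is not random.

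**Little depends on it.** The promising/not-promising decision sets TKM patients against a fixed 0.55, the observational aim is descriptive, and no formal comparison is planned. This stands and limits the severity.

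**Adding the missing patients does not give mortality for all admissions.** TKM patients are outside the observational group by design, and pooling eligible with ineligible patients still blurs the result. This also stands, and it is why the estimates should be reported separately as well.

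A reader might also infer that the reported mortality is biased upward, since patients for end-of-life care only and those without IV access are added. The documents do not support that. The same rule adds late transfers and others already recovering (7.4, 7.5). It adds under-18s, whose case fatality by section 12.1 is highest below age 5 and lowest at about 15-20 years. It adds refusers of unknown mortality. The 48-hour restriction also removes some of the sickest.

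The capacity exit in Figure 2 reads "Insufficient operational capacity. Patient will receive standard care" with no mention of anonymised data, unlike the stage 1 exit. The figure was read by a program and its arrows are unclear, so the point rests on the text of 7.4 and 7.5.

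**Conclusion.** The gap is real in v2.9. Stage-1-eligible patients without a bed in either cohort belong to no analysis, while all ineligible patients and refusers enter the observational primary analysis. The observational D14 mortality therefore over-weights the latter by an amount set by bed capacity.

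Neither direction nor size can be fixed from the documents. Under the assumptions above the shift is −0.043 to +0.057 when half the eligible off-drug patients get a bed, and −0.098 to +0.131 when a fifth do. It is zero if the cap never binds or if the two groups have equal mortality. How often the cap would bind is not stated. The TKM conclusion is untouched. This should be mended, but it does not threaten the trial's main decision.

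**What to change.** In section 7.5, extend the anonymised D14 data in the observational primary analysis to all stage-1-eligible patients who were allocated to neither cohort because of capacity. Then:

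- flag TKM-eligible non-allocated patients and stage 2 failures separately;
- report the estimate for TKM-eligible non-allocated patients apart from that for ineligible patients and refusers;
- label the capacity exit in Figure 2 to match.

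The cost is a short addition to 7.5, one figure label and a flag in the data. Survival is already collected under section 9.1. The added patients would have survival data only, as do the ineligible patients already included.

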## **8. TRIAL PROCEDURES**

### **8.1. Screening and informed Consent**

Patients with RT-PCR confirmed Ebolavirus RNA (confirmed patients) will be screened for trial eligibility and invited to give informed consent to participate, according to the procedures outlined in section 15.2. Staff will not discuss informed consent with patients (or the parents/representatives of patients <18 years old) who are not eligible for enrolment in any trial arm. The number of patients who are ineligible will be recorded anonymously. Study dosing, sampling and data collection will begin only after enrolment.

A patient may be consented to take part in the study anytime within 48 hours of first arriving at the ETC with a confirmed diagnosis, or, within 48 hours of being informed of Ebolavirus positive PCR result, if this occurs while already at the centre. Therefore, if a patient has been excluded for a reason that resolves within this period, they may be approached upon resolution of the reason for exclusion. If a patient wishes to delay their decision regarding consent, they may consent at any time within the 48 hour period.

Whenever possible, patient dosing will be started within 2 hours of the trial team arrival in the morning, in order to provide adequate time for patient monitoring and to complete the required post dose assessments. The actual time of dosing will depend on various factors, including number of patients on the study and staffing levels in the ETC. Consent and any randomisation will need to be completed before this time. If a patient chooses to delay consent, or consent cannot be obtained e.g. family or proxy not available, consent and randomisation of other patients will proceed. Any patients who cannot consent will be considered for enrolment the following day if this is still within the required 48 hour window.

A list of eligible patients will be produced each day (following receipt of the laboratory results).

Once the randomisation process is complete, to either the TKM treatment or observational cohorts, re-randomisation is not permitted.

### **8.2. In-patient Days**

Standard safety assessments of patients will include daily monitoring of vital signs (pulse rate, blood pressure, respiratory rate, temperature), symptoms and SARs whilst they remain in the ETC. Any non-study medication received will also be recorded.

In addition, for the TKM treatment cohort, vital signs and assessment of possible infusion related reactions will be assessed at the following approximate time points: pre-infusion, during the infusion (preferably between 30-90 minutes), at the end of infusion (0 hour), and at 1, 2, 4 and 8 hours post end of infusion, as well as at additional time points if indicated by the patient's clinical condition.

The recruitment process for the safety cohort is described in Section 7.4. The IDMC will review data from the safety cohort prior to recruitment being opened to all eligible patients. The safety cohort may be expanded following advice from the IDMC.

